### Outcomes

The primary outcome is treatment failure, defined as intubation and invasive ventilation, or a switch in respiratory support modality (i.e., changing from HFNC to NIV or vice-versa). Detailed information about treatment failure will be recorded from baseline to 28 days after randomization. Secondary outcomes include arterial blood gas (ABG) analysis results [pH, PaO_2_, PaCO_2_, and PaO_2_/FiO_2_] and vital signs [respiratory rate, heart rate, and blood pressure] at 2 and 12 h after initiating NIV or HFNC, as well as the patients’ comfort scores, dyspnea scores, the daily number of nursing airway care interventions, the incidence of pneumonia or pneumothorax, skin breakdown related to the airway device, duration of NIV or HFNC, total ICU and hospital lengths of stay, and 28-day mortality.

In the initial trial registry entry, we set arterial blood gas analysis results and vital signs as the primary outcomes. Considering that the primary purpose of this study was to compare the efficacy and safety of HFNC and NIV for BCT patients, we changed the primary endpoint to treatment failure before starting patient enrollment. The amendments were approved by the study’s steering committee and the ethics review committee of Northern Jiangsu People’s Hospital.

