**Methods:**

This will be a prospective, open-label, multicenter, non-inferiority, randomized controlled trial. Moderate to severe BCT patients with acute respiratory failure (100mmHg < PaO_2_/FiO_2_ ≦ 200mmHg) who do not need immediate intubation will be randomized to HFNC or NIV within 48 h after trauma. The primary outcome is treatment failure, defined as invasive ventilation or a switch in respiratory support modality (from HFNC to NIV or vice-versa). Secondary outcomes include arterial blood gas analysis and vital signs at 2 and 12 h after initiating HFNC or NIV treatment, as well as patients’ comfort scores, dyspnea scores, daily number of nursing airway care interventions, incidence of pneumonia or pneumothorax, facial skin breakdown, duration of NIV or HFNC, 28-day mortality, and total ICU and hospital lengths of stay. Based on an *α* error of 5% and a *β* error of 80%, with a non-inferiority limit of 9%, a sample size of 562 will be required to accomplish the trial goal, considering potential patient dropouts and nonparametric analysis.

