## Background

Blunt chest trauma (BCT) is a common traumatic injury, especially common in motor vehicle collisions or falls. Mortality due to BCT can be as high as 36% and is the second-leading cause of death in trauma after head injuries [1]. Acute respiratory failure is an important cause of death in patients with BCT. Fifty to 70% of chest trauma is accompanied by acute respiratory failure, and up to 20% develop acute respiratory distress syndrome [2, 3].

Invasive mechanical ventilation is recommended for severe BCT patients with decreased levels of consciousness, significant respiratory distress, airway obstruction, severe hypoxemia, or hemorrhagic shock. However, for moderate to severe BCT patients not accompanied by the above-mentioned conditions, invasive ventilation may increase the incidence of hospital-acquired pneumonia and prolong the duration of mechanical ventilation and intensive care unit (ICU) length of stay, all of which can lead to worse outcomes [4].

In recent years, several studies have found that noninvasive ventilation (NIV) had a beneficial effect on BCT patients with acute respiratory failure. Two randomized controlled studies found that for flail chest or multiple rib fractures with respiratory failure, NIV reduced mortality and the incidence of pneumonia by 28% and 34%, respectively, compared with invasive mechanical ventilation [5, 6]. In a randomized controlled trial comparing NIV to standard oxygen therapy in patients with a ratio of PaO_2_ to the fraction of inspired oxygen (FiO_2_) [PaO_2_/FiO_2_] less than 200 mmHg within 48 h after BCT, early continuous use of NIV significantly reduced the rate of intubation compared to standard oxygen therapy alone (12% vs 40%) and shortened their hospital stay by as much as 7 days [7].

A meta-analysis also showed that for BCT patients with intact neurological function, stable hemodynamics, and no obvious respiratory distress, early NIV could significantly reduce the rate of endotracheal intubation and complications, as well as shorten the hospital length of stay, with a NIV failure rate of only 12–18% [8]. However, patients with BCT often have facial injuries, which is a contraindication to NIV. In addition, about 15% of patients cannot tolerate NIV [9]. NIV intolerance may lead to increased rates of treatment failure and affect the overall clinical outcome.

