Patients in both groups will be in a semi-recumbent position unless contraindicated. A multi-modal pain control regimen will be adopted in all participants. Epidural analgesia with sufentanil plus bupivacaine will be preferred, combined with oral celecoxib (200 mg twice daily). When the visual analogue scale of pain is greater than 6, 100 mg tramadol will be given intravenously as a remedial treatment. For patients with contraindications to regional anesthesia (acute spine fracture, unstable pelvic fracture, coagulopathy, et al.), analgesia based on intravenous remifentanil will be administered, and the dosage will be determined using pain scales. In addition to respiratory support and pain management, other treatments will be supplied to both groups according to current guidelines, including hemostasis, external fixation of the chest wall, thoracentesis or thoracic closed drainage, fluid resuscitation, blood transfusion, or any surgical operation, if necessary [15].

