Furthermore, we will also record any episodes of endotracheal intubation, or switching of respiratory support modality, including the reason and time for these events. We will also document any diagnosed episodes of pneumothorax or pneumonia, as well as each patients’ length of stay in the ICU and hospital, and their 28-day mortality.

Any decision to intubate a patient will be made by the patient’s attending physician. Criteria for intubation in this trial are cardiac arrest or apparent hemodynamic instability, significant hypoxemia (SpO_2_ < 85% while under sufficient oxygen therapy), respiratory acidosis with a pH < 7.25 under optimal medical management, severe disturbances of consciousness (Glasgow score <11), obvious aspiration or significantly reduced capacity for airway protection, active use of accessory muscles with thoraco-abdominal paradoxical movements, severe dyspnea (respiratory rate > 40 per minute), or respiratory depression (respiratory frequency < 8 per minute) [7].

All data will be collected on paper case report forms (CRFs) from patients’ electronic medical records. The data manager will collect CRFs and enter data to a dedicated web-based electronic database in de-identified form. The electronic data will be backed up, and the backed-up electronic data will be kept secure by the sponsor. The sponsor will check the data again according to the CRFs to ensure data accuracy. Treatment allocation will be anonymously processed to allow the independent statistician in this trial to be blinded. Only the trial investigators will have access to the final dataset.

The sponsor and statisticians will have access to the preliminary data set to enable needed statistical work. Doctors authorized by the sponsor will have access for data entry and for reviewing data at their site. Participants will be allocated an individual trial identification number and the allocation information will be stored in a separate, secure database. All data will be kept confidential and will not be disclosed. Anonymized trial data will be shared with other researchers upon reasonable request to contribute to future international prospective meta-analyses.

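### The primary outcome has no death component, so a patient who dies within 28 days without intubation or a modality switch counts as a non-failure

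*Protocol article*

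**What the plan says.** The definition appears in full twice, with the same two components. The Abstract (Methods) has: "The primary outcome is treatment failure, defined as invasive ventilation or a switch in respiratory support modality". The Outcomes section has: "The primary outcome is treatment failure, defined as intubation and invasive ventilation, or a switch in respiratory support modality". The window is 28 days: "Detailed information about treatment failure will be recorded from baseline to 28 days after randomization". Death appears only at the end of the list of secondary outcomes: "total ICU and hospital lengths of stay, and 28-day mortality".

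The section on statistical analysis and sample size builds its planning rate the same way. It starts from reported intubation rates of 12–18% on NIV and assumes 18–23% once modality switches are included. Death is not mentioned. The margin is 9 percentage points, α is 0.05 one-sided, and the target is 562 patients (281 per arm).

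The decision to intubate lies with the attending physician, who is not blinded. The Data collection and management section lists when to intubate: "Criteria for intubation in this trial are cardiac arrest or apparent hemodynamic instability, significant hypoxemia", followed by further respiratory, consciousness and airway criteria. The reason and time of each intubation or switch are recorded, but no rule in the article uses the reason to classify the outcome.

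**The concern.** The Outcomes section says the primary endpoint was changed to treatment failure because the trial is meant to compare efficacy and safety. On the literal definition, the worst outcome a patient can have does not count as failure unless an intubation or a switch came first.

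In a superiority trial, leaving out a bad outcome may only cost sensitivity. In a non-inferiority trial the direction matters more. If such deaths were more frequent on HFNC, the primary comparison would not register the excess. If some of those patients would otherwise have gone on to intubation, their deaths would even lower the HFNC failure rate. Either way, the claim of non-inferiority would be easier to make than it should be.

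**Working it through.** **Inputs from the article.** Margin 0.09, one-sided α 0.05, power 0.80, failure rate 18–23% in each group, 488 patients before inflation, 562 after (281 per arm).

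**Inputs that are assumptions.** The rate of death within 28 days without intubation or switch is not given. I take 1% on NIV with an HFNC excess of 1, 2 or 3 points and, for contrast, 2% in both arms. Failure as written is held at 20% in both arms. Non-inferiority is taken as claimed when the upper one-sided 95% limit for HFNC minus NIV lies below 0.09.

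**Step 1: reproduce the plan's figure.** With equal rates p, total N = 2 × 2p(1−p)(1.645 + 0.842)² / 0.09². At p = 0.20 this is 4 × 0.16 × 6.183 / 0.0081 = 488.5, which matches 488. Then 488 × 1.15 = 561.2, which rounds up to the even total of 562. The sample size is not in error, and 20% is a fair base rate for what follows.

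**Step 2: chance of claiming non-inferiority.** With n = 281 per arm,

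SE = √[p_N(1−p_N)/n + p_H(1−p_H)/n], and the chance is Φ[(0.09 − (p_H − p_N))/SE − 1.645].

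As written, p_N = p_H = 0.20: SE = 0.03375, 0.09/SE = 2.667, and Φ(1.022) = 84.7%. Deaths without an event do not enter, so this figure is the same whatever their excess on HFNC.

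**Step 3: count those deaths as failures.** The death rate is added to the 20%.

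| Deaths without event, NIV / HFNC | Failure rate, NIV / HFNC | SE | Φ argument | Chance of claim |
|---|---|---|---|---|
| 1% / 2% | 21% / 22% | 0.03466 | 0.664 | 74.7% |
| 1% / 3% | 21% / 23% | 0.03494 | 0.359 | 64.0% |
| 1% / 4% | 21% / 24% | 0.03521 | 0.059 | 52.4% |
| 2% / 2% | 22% / 22% | 0.03495 | 0.930 | 82.4% |

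Against 84.7% as written, the first three rows show what an HFNC excess does when it is allowed to count. The last row shows that deaths balanced between the arms cost about 2 points of power and nothing else.

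**The case against.** **Some deaths are caught already.** Cardiac arrest is the first listed intubation criterion, so many patients who arrest will be intubated and counted. This stands and narrows the gap. It does not close it: a criterion does not guarantee that the tube is placed, and the 28-day window can run past ICU discharge. The article has no rule for a death that escapes.

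**Mortality is reported anyway.** It is a prespecified secondary outcome, so an excess would be visible. That is true, but the non-inferiority margin is attached to treatment failure alone, and the claim would be made on that.

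**The effect depends on imbalance.** This is correct. One could construct a starker case: failure at 20% v 24% with uncounted deaths of 2% v 4% gives 41.6% as written and 20.6% with deaths counted. With equal deaths of 2% the same case moves only from 41.6% to 39.9%, so nearly all of the drop is the assumed imbalance. The article's only comparative mortality evidence, a multicenter study in hypoxic respiratory failure cited in the Discussion, favours HFNC, though in a different population.

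**Two stronger readings that the article does not support.** The Background says "Mortality due to BCT can be as high as 36" per cent, and a reader might take that as the scale of the problem. It is an upper figure for blunt chest trauma in general. This trial excludes patients who need immediate intubation, are haemodynamically unstable or have a Glasgow score below 11, and the figure says nothing about deaths without intubation or switch.

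A reader might also infer that intubation for an operation is wrongly scored as failure. The Study groups section does allow "fluid resuscitation, blood transfusion, or any surgical operation, if necessary" in both arms, and the definition does not limit intubation by reason. However, an operation is not among the listed intubation criteria, and the reason is recorded. The article does not state the classification, so this is an ambiguity and not a demonstrated misclassification. Excluding events on a reason given by unblinded physicians would also carry its own risk.

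**Conclusion.** The point holds for death. Both statements of the primary outcome omit it, and a death within 28 days without intubation or switch is a non-failure. The size cannot be derived from the article. Under the stated assumptions, an HFNC excess of 1 to 3 points in such deaths leaves the chance of a non-inferiority claim at about 85%, where counting the deaths would bring it to about 75%, 64% or 52%. If the deaths are balanced, the omission hardly matters. This is a flaw in how the outcome protects the claim. It is not evidence that such an excess exists or that the sample size is wrong. On operative intubation, the only supportable conclusion is that the passages need to be reconciled.

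**What to change.** Count death from any cause within 28 days of randomization, without a prior intubation or switch, as treatment failure in the primary outcome. The Trial status section shows recruitment well advanced, and the primary endpoint was already changed once before enrolment. If a further amendment is not acceptable, prespecify, before the statistician is unblinded, a death-inclusive analysis that must also meet the 9-point margin for non-inferiority to be claimed. Because both analyses must succeed, this does not inflate the type I error.

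No new data are needed, since 28-day mortality and the time of each intubation or switch are already collected. The cost is a slightly higher event rate and slightly lower power. With such deaths at 2% in both arms, power at 281 per arm goes from 84.7% to 82.4%, and the formula in Step 1 gives 524 before inflation instead of 488. The planning rate should be restated to match.

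Separately, reconcile Study groups, Outcomes, and Data collection and management with one sentence saying whether an intubation outside the listed criteria, for example for an operation, counts as treatment failure.

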### Data collection and management

We will collect the personal characteristics of each BCT patient (age, gender, height, and weight), medical history, time of traumatic injury, mechanism of injury, injured organs, imaging results, injury severity score (ISS), AIS chest score, and Sequential Organ Failure Assessment (SOFA) score at enrollment. In addition, we will also collect vital signs (respiratory rate, heart rate, and blood pressure), comfort score, dyspnea score, and ABG results from just prior to initiating HFNC or NIV treatment after patient enrollment (see Table 1). Patients’ dyspnea will be evaluated using the Borg rating scale [16], and patients’ comfort score will be assessed using a 10-cm visual analogue scale, in which 1 means no discomfort and 10 means maximal discomfort [17].

**Table 1 Tab1:** Schedule of enrolment, interventions, and assessments

	Study period					
	Enrolment	Allocation	Post-allocation			Close-out
Timepoint	0	0	2 h	12 h	1–28 days maximum	28 days maximum
Enrolment						
Eligibility screen	×					
Informed consent	×					
Allocation		×				
Interventions						
NIV		×				
HFNC		×				
Assessments						
Baseline variables						
Demographics	×					
Medical history	×					
Mechanism of injury	×					
Injury severe score	×					
Chest AIS score	×					
SOFA score	×					
Outcome variables						
Intubation			×	×	×	
Treatment switch			×	×	×	
Vital signs		×	×	×	×	
Comfort score		×	×	×	×	
Dyspnea score		×	×	×	×	
Arterial blood gas		×	×	×	×	
Number of nursing airway care interventions					×	
Pneumonia or pneumothorax					×	
Skin breakdown					×	
Causes of treatment failure						×
NIV/HFNC duration						×
Hospital length of stay						×
ICU length of stay						×
28-day mortality						×

*HFNC* high-flow nasal cannula oxygen therapy, *NIV* noninvasive ventilation, *AIS* Abbreviated Injury Scale, *SOFA* Sequential Organ Failure Assessment, *ICU* intensive care unit

At 2 and 12 h after allocation, vital signs, ABG results, comfort score, and dyspnea score will be collected. We will then re-collect this information every day until ICU discharge. Moreover, we will separately record each patient’s HFNC or NIV settings, any episodes of skin breakdown related to the airway interface, the number of nursing airway care interventions, and any intolerance to HFNC or NIV due to claustrophobia, excessive air flow or pressure, breathlessness, noise, ocular irritation, headache, or other reasons.

Furthermore, we will also record any episodes of endotracheal intubation, or switching of respiratory support modality, including the reason and time for these events. We will also document any diagnosed episodes of pneumothorax or pneumonia, as well as each patients’ length of stay in the ICU and hospital, and their 28-day mortality.

Any decision to intubate a patient will be made by the patient’s attending physician. Criteria for intubation in this trial are cardiac arrest or apparent hemodynamic instability, significant hypoxemia (SpO_2_ < 85% while under sufficient oxygen therapy), respiratory acidosis with a pH < 7.25 under optimal medical management, severe disturbances of consciousness (Glasgow score <11), obvious aspiration or significantly reduced capacity for airway protection, active use of accessory muscles with thoraco-abdominal paradoxical movements, severe dyspnea (respiratory rate > 40 per minute), or respiratory depression (respiratory frequency < 8 per minute) [7].

All data will be collected on paper case report forms (CRFs) from patients’ electronic medical records. The data manager will collect CRFs and enter data to a dedicated web-based electronic database in de-identified form. The electronic data will be backed up, and the backed-up electronic data will be kept secure by the sponsor. The sponsor will check the data again according to the CRFs to ensure data accuracy. Treatment allocation will be anonymously processed to allow the independent statistician in this trial to be blinded. Only the trial investigators will have access to the final dataset.

The sponsor and statisticians will have access to the preliminary data set to enable needed statistical work. Doctors authorized by the sponsor will have access for data entry and for reviewing data at their site. Participants will be allocated an individual trial identification number and the allocation information will be stored in a separate, secure database. All data will be kept confidential and will not be disclosed. Anonymized trial data will be shared with other researchers upon reasonable request to contribute to future international prospective meta-analyses.

### Statistical analysis and sample-size calculation

Reported intubation rates in BCT patients receiving NIV range from 12 to 18% [8], so the sample size is estimated assuming a baseline failure rate (including modality switch) of 18–23% for each group and a predefined non-inferiority margin of 9% for HFNC. We set the non-inferiority margin according to relevant data [18, 19], and after discussion with three senior pulmonologists. We computed a sample size of 488 patients in this trial, using an *α* = 0.05 (one-sided) and *β* = 0.20, with a non-inferiority limit of 9%. After considering a potential patient dropouts and nonparametric analysis, 562 patients (281 per modality) will be the target sample size for this trial.

All statistical analyses will be performed on an intention-to-treat basis by an independent investigator who is blinded to treatment allocation. The Kolmogorov–Smirnov test will be used to test the normal distribution of data. Normally distributed data will be expressed as means ± standard deviation, while skewed distributed data will be reported as medians with interquartile (25th–75th) percentiles. The two modality groups will be compared using *t*-tests or Mann–Whitney *U*-tests. Numeric data will be presented as a percentage (%), using chi-squared or Fisher’s exact probability tests. Significance will be set at < 0.05 and all data analysis will be conducted with SPSS 26.0 (IBM Corporation, Armonk, NY, USA).

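### The computed 488 patients give the stated 80% power only up to a failure rate of about 20%, not across the assumed 18–23%, and the abstract gives the beta error as 80%

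*Protocol article*

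**What the plan says.** The section on statistical analysis and sample-size calculation gives the design rate as a range: "assuming a baseline failure rate (including modality switch) of 18–23% for each group". It adds "a predefined non-inferiority margin of 9% for HFNC" and then a single result: "We computed a sample size of 488 patients in this trial". One-sided alpha is 0.05 and beta is 0.20. The increase to the final number is explained as follows: "After considering a potential patient dropouts and nonparametric analysis, 562 patients (281 per modality) will be the target sample size". The section does not say which rate within the range produced 488.

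The Methods paragraph of the abstract describes the same design differently: "Based on an *α* error of 5% and a *β* error of 80%, with a non-inferiority limit of 9" per cent, leading to 562. It does not say that alpha is one-sided.

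Under Outcomes, the primary endpoint is treatment failure (intubation with invasive ventilation, or a switch of modality), recorded to 28 days. It is therefore a binary outcome. The statistical section assigns percentages to chi-squared or Fisher's exact tests and plans intention-to-treat analysis.

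**The concern.** For a fixed margin, the sample size needed for a difference in proportions rises with the failure rate over this range. A number that gives 80% power at the lower or middle part of 18–23% will not give it at the top. The text presents 488 as the answer for the range without saying where in the range it applies.

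Two further statements in the same calculation look wrong. A beta error of 80% is a power of 20%, which contradicts beta = 0.20 in the body. An allowance for nonparametric analysis belongs to rank tests on continuous outcomes and has no role in sizing a comparison of two proportions.

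What is at stake is how the result will be read. If this non-inferiority trial is inconclusive, readers will judge that against the stated power, so the stated power should be correct, consistent between abstract and body, and tied to a named failure rate.

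**Working it through.** **Inputs**, all from the statistical section unless noted: equal true failure rate p in both groups, 18–23%; margin 0.09, read as an absolute difference; one-sided alpha 0.05 (z = 1.645); beta 0.20 (z = 0.842); 1:1 allocation (Design and setting); 488 before and 562 after inflation, that is 244 and 281 per arm.

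**Reproducing 488.** With unpooled variance and no true difference,

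n per arm = (1.645 + 0.842)² × 2p(1 − p) / 0.09²

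- p = 0.18: 225.3, so 226 per arm, 452 in total
- p = 0.20: 244.25, so 245 per arm, 490 in total
- p = 0.205 (midpoint of the range): 498 in total
- p = 0.23: 270.4, so 271 per arm, 542 in total

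The plan's 488 is 2 × 244, the 20% result without rounding up. Solving the formula for exactly 244 per arm gives p = 19.97%. So 488 reproduces, at a rate of about 20%.

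**Power at the stated numbers.** Power = Φ(0.09 / √(2p(1 − p)/n) − 1.645).

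| Failure rate, both groups | Total needed for 80% | Power, 488 analysed | Power, 562 analysed |
|---|---|---|---|
| 18% | 452 | 82.7% | 87.1% |
| 20% | 490 | 80.0% | 84.7% |
| 21% | 508 | 78.7% | 83.5% |
| 22% | 524 | 77.5% | 82.4% |
| 23% | 542 | 76.3% | 81.3% |

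Worked line for 23% with 244 per arm: √(2 × 0.23 × 0.77 / 244) = 0.0381; 0.09 / 0.0381 = 2.362; 2.362 − 1.645 = 0.717; Φ(0.717) = 76.3%. The shortfall is 3.7 points of power, or 542 − 488 = 54 patients.

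**Loss that 562 can absorb.** The implied allowance is 1 − 488/562 = 13.2% (equivalently 488 × 1.15 = 561.2, rounded up to 562). The loss at which power falls to 80% is:

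- at 21%: 1 − 508/562 = 9.6%
- at 22%: 1 − 524/562 = 6.8%
- at 23%: 1 − 542/562 = 3.6%

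**Other readings of the calculation.**

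- The Farrington–Manning method gives 458, 494 and 544 at 18%, 20% and 23%.
- A continuity correction gives 496, 534 and 586.
- Taking 18% and 23% as the rates of different arms gives 2,510 in total (HFNC at 23%) or 206 (HFNC at 18%).

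None of the equal-rate methods makes 488 sufficient at 23%, and the unequal-rate readings come nowhere near 488.

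**Abstract against body.** The body has beta 0.20, hence 80% power. The abstract's 80% is evidently the power labelled as beta. Its omission of one-sidedness also matters for anyone checking the number: at one-sided 0.025 and a 20% rate, the same formula gives 622.

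**The case against.** The strongest reply is that the trial aims to recruit 562, not 488. With 562 analysed, power exceeds 80% at every rate in the range. Analysis is by intention to treat on an endpoint recorded to 28 days, so heavy loss is not a given. Even in the worst corner, 23% with the full 13.2% lost, power is 76.3%. This stands, and it limits the point: a reader might infer that the trial is underpowered, but the article's own figures do not support that unless a rate above about 20% and material losses occur together.

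A reader might also infer that 488 is a miscalculation. It is not: it is right at about 20%, and both the midpoint of the range (498) and a continuity-corrected calculation at 18% (496) come close. A single number can properly be drawn from a range by designing at a chosen value; the fault is that the value is not stated and the power claim is not limited to it. Nor can 20% be asserted as the rate the sponsor used, because the article names neither the rate nor the formula.

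It may be said that nonparametric analysis refers to the Mann–Whitney tests planned for other outcomes, and that the inflation only adds patients. It does no harm to power, but it remains a wrong reason for enlarging a sample sized on the primary outcome. How the roughly 15% divides between its two stated causes is detail that a condensed article may leave to the full protocol, and it is not part of this point.

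Finally, the abstract's beta is contradicted by the explicit value in the body and does not alter the sample size. That is true, but it is still a wrong statement of a core design parameter.

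**Conclusion.** The point holds as a correction of stated figures, not as a design failure. With one-sided alpha 0.05, an absolute 9% margin, equal true rates and the normal approximation, 488 evaluable patients deliver the stated beta of 0.20 only up to a failure rate of about 20%. At the upper end of the article's own range, power is 76.3% and 542 evaluable patients would be needed. The recruitment target of 562 covers the whole range if all are analysed (81.3% at 23%), and at 23% it keeps 80% power only while losses stay within about 3.6%.

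Separately, the abstract's beta error of 80% contradicts the body. Read literally it describes a trial with 20% power, a reading the body's beta = 0.20 and the reproduced 488 rule out. The reference to nonparametric analysis does not justify enlarging a sample sized on a binary endpoint.

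**What to change.** Four changes of wording:

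1. In the abstract, give beta as 20% (power 80%) and state that the 5% alpha is one-sided.
2. In the statistical section, have the sponsor state the single failure rate behind 488. Back-calculation points to about 20% in both groups; the sponsor must confirm this.
3. Report power across the range at both numbers: with 488 evaluable, 82.7% at 18%, 80.0% at 20% and 76.3% at 23%; with all 562 analysed, 87.1%, 84.7% and 81.3%.
4. Drop nonparametric analysis as a reason for the primary-outcome sample size.

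The cost is text only, with no change in enrolment, margin or alpha. The downside is that the stated power looks slightly less favourable at the upper end of the range.
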